#### Statistical methods

The principal analysis will be done on an intention-to-treat basis; outcome measures will be analyzed according to the treatment arm to which patients are randomized regardless of subsequent crossover or non-adherence. To model the outcome variables over time, we will use a linear mixed effects model [39]. Age, parity, and BMI will be considered as potential covariates to improve precision. We will also do post-hoc comparisons of time points within groups, looking at within-group changes in outcome variables from gestational week 14 to 37, as well as from gestational week 37 to 12 weeks post partum.

In addition to the primary analysis, we will split the women according to if they have actually been exercising during pregnancy or not. The cut-off for this analysis will be: 1) attending  $\geq 42$  organised exercise sessions, or 2) attending  $\geq 28$  exercise sessions + performing  $\geq 28$  home exercise sessions, or 3) performing  $\geq 60$  home exercise sessions. To count as a home exercise session, the exercise should be  $\geq 50$  minutes (either aerobic or strength training) of at least moderate intensity. We also intend to compare women fulfilling the general recommendations for healthy adults of exercising moderately for 30 minutes daily [40], with the ones below this threshold. Results will be given as mean values with 95% confidence intervals. P-values  $< 0.05$  will be considered significant.

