# Exercise Training in Pregnancy for obese women (ETIP): study protocol for a randomised controlled trial

[name]1,3\*, [name], [name], [name], [name] and [name]

**Background:** Both maternal pre-pregnancy obesity and excessive gestational weight gain are increasing in prevalence and associated with a number of adverse pregnancy outcomes for both mother and child. Observational studies regarding physical activity in pregnancy have found reduced weight gain in active mothers, as well as reduced risk of adverse pregnancy outcomes. There is however a lack of high quality, randomized controlled trials on the effects of regular exercise training in pregnancy, especially those with a pre-pregnancy body mass index (BMI) at or above 30 kg/m^2.

**Methods:** We are conducting a randomised, controlled trial in Norway with two parallel arms; one intervention group and one control group. We will enroll 150 previously sedentary, pregnant women with a pre-pregnancy BMI at or above 30 kg/m^2. The intervention group will meet for organized exercise training three times per week, starting in gestation week 14 (range 12-16). The control group will get standard antenatal care. The main outcome measure will be weight gain from baseline to delivery. Among the secondary outcome measures are changes in exercise capacity, endothelial function, physical activity level, body composition, serum markers of cardiovascular risk, incontinence, lumbopelvic pain and cardiac function from baseline to gestation week 37 (range 36-38). Offspring outcome measures include anthropometric variables at birth, Apgar score, as well as serum markers of inflammation and metabolism in cord blood.

**Discussion:** The results of this trial will provide knowledge about effects of regular exercise training in previously sedentary, obese pregnant women. If the program proves effective in reducing gestational weight gain and adverse pregnancy outcomes, such programs should be considered as part of routine pregnancy care for obese women.

**Trial Registration:** ClinicalTrials.gov: NCT01243554

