#### Sample size

Based on prior studies [37,38], the power calculation has taken into account a 6 kg expected and clinically relevant difference between mean weight increases in the control group compared to the training group (between baseline and delivery). Based on this assumption, an independent samples t-test, 5% level of significance and test strength of 0.90, gives a study population of 59 in each group. A 15% estimated drop-out requires a total of 150 included obese pregnant women, 75 enrolled in each arm.

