Strengths of our study include the thorough testing that will be done of the women as well as their offspring; investigating possible effects of exercise training on weight gain, endothelial function, insulin resistance, cardiac function, incontinence problems, lumbopelvic pain, and psychological wellbeing. In addition we collect comprehensive information on physical activity, using both subjective and objective measurements (questionnaire and armband activity registrations, respectively), as well as on dietary habits. Also regarded as a strength of the study, is the composition of the exercise training program, comprising both endurance training, general strength training and specific pelvic floor exercises.

A possible weakness of our study is that it could be underpowered for small differences in gestational weight gain between groups. Also, we think that women who like to participate in this kind of study are motivated for exercise and thereby that some of the women in the control group will do regular exercise training on their own. Such cross-over from the control group would potentially lead to smaller between-group differences.

The results from our study will give grounds for giving advice as well as organizing exercise training groups for women with obesity entering pregnancy. If women randomized to training manage to reduce their gestational weight gain compared to controls, such programs should be considered as part of the regular pregnancy care for this high-risk obstetric group.

In addition to effects on weight gain, we hope to see a reduction in other pregnancy complications. Our study will investigate the ability of regular exercise training to prevent gestational diabetes mellitus, as well as the effect on serum biomarkers associated with insulin resistance and inflammation. Previous work have found that exercise training may reduce lumbopelvic pain [46,47], however, a preventive effect of exercise during pregnancy remains unclear. Pregnancy and childbirth may also cause urinary and fecal incontinence, and obesity is an additional risk factor. The average prevalence of

urinary incontinence during pregnancy and after delivery is 30-40%, and of fecal incontinence after delivery 4-5% [48]. Specific pelvic floor muscle exercises in pregnancy and post partum reduce urinary incontinence, while the preventive effect on fecal incontinence is less documented [49].

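### The protocol's single significance rule (P below 0.05) covers dozens of secondary outcomes and post-hoc comparisons as well as the one primary outcome, so some chance findings would be called significant

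*Protocol*

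**What the plan says.** The protocol names one primary outcome, gestational weight gain (Primary outcome measure), and bases its sample size on that outcome alone, with a "5% level of significance and test strength of 0.90".

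The secondary outcomes are numerous. The abstract gives a partial list: "Among the secondary outcome measures are changes in exercise capacity, endothelial function, physical activity level, body composition, serum markers of cardiovascular risk", and continues with incontinence, lumbopelvic pain, cardiac function and offspring measures. The Secondary outcome measures section expands this to glucose and blood markers, skinfolds and DEXA, pain tests, pelvic floor measures, several questionnaires, blood pressure, endothelial function, echocardiography, treadmill tests, delivery variables and a long offspring list. No total is given. The Objectives section attaches directional hypotheses of benefit to many of these, among them pregnancy complications, physical capacity, endothelial function, blood pressure, large-for-gestational-age prevalence, cord blood markers and Apgar score.

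Statistical methods treats outcomes generically: "outcome measures will be analyzed according to the treatment arm to which patients are randomized". It adds post-hoc within-group comparisons over two intervals, a split by whether women actually exercised, and a second split by a daily activity recommendation. The section then closes with the reporting rule: "Results will be given as mean values with 95% confidence intervals", and P-values below 0.05 "will be considered significant". The rule is not limited to any class of outcome.

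**The concern.** A protocol may leave the treatment of secondary outcomes to the statistical analysis plan. This one instead states a rule, and read literally that rule makes any secondary, within-group or exercise-split result with P below 0.05 a significant finding, on the same footing as the primary comparison. No adjustment, hierarchy or exploratory label qualifies it.

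With several dozen tests at that level, a few will cross the threshold by chance even if exercise affects none of these outcomes. Many of the outcomes carry a stated hypothesis of benefit, so a chance result in the expected direction would read as confirmation. What is at stake is the strength of claims about secondary outcomes, not the validity of the primary test.

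**Working it through.** **Figure in the plan.** The protocol states no familywise error rate and no expected number of false positives, so there is no figure of its own to reproduce on this point.

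**Inputs.**
- Threshold: 0.05 per test (Statistical methods). Sidedness is not stated; two-sided is assumed, so 0.025 lies in the direction favouring exercise.
- Number of secondary outcomes, m: counted by reading Objectives and Secondary outcome measures, with grouped items such as lipids or Doppler flow counted once. This gives about 41 maternal items and 18 offspring items at birth and in the newborn period: 41 + 18 = 59. About 5 items from the 3- and 12-month child follow-up bring it to 64. A stricter reading that drops items which need not be efficacy tests gives a smaller number. I use m = 50 as a working value, with 40 and 64 as the range.
- Not counted: repeated time points, within-group comparisons and the two exercise splits.
- Correlation between test statistics: not given. Common values of 0.3 and 0.5 are assumed beside independence.
- All nulls are taken as true, to show what chance alone produces.

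**Expected number** (does not depend on correlation):
- Either direction: m × 0.05 = 50 × 0.05 = 2.5
- Favouring exercise: m × 0.025 = 50 × 0.025 = 1.25

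**Chance of at least one, independent tests:**
- Either direction: 1 − 0.95^50 = 0.923
- Favouring exercise: 1 − 0.975^50 = 0.718

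**With correlation.** For equicorrelated standard normal statistics, Z_i = √ρ·U + √(1−ρ)·E_i. The chance of at least one is 1 minus the probability that no |Z_i| (or, for the favourable direction, no Z_i) exceeds 1.96, averaged over U. Simulation and numerical integration agree to within sampling error.

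| m | Expected (either / favourable) | Either direction: independent, ρ 0.3, ρ 0.5 | Favouring exercise: independent, ρ 0.3, ρ 0.5 |
|---|---|---|---|
| 40 | 2.0 / 1.0 | 87%, 75%, 57% | 64%, 40%, 29% |
| 50 | 2.5 / 1.25 | 92%, 81%, 62% | 72%, 45%, 32% |
| 64 | 3.2 / 1.6 | 96%, 86%, 68% | 80%, 49%, 35% |

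If the tests were one-sided at 0.05 in the direction of benefit, the expected number of favourable chance results at m = 50 would be 2.5 rather than 1.25.

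**The case against.** **The protocol does separate primary from secondary outcomes.** It does so in the abstract, the Objectives, the outcome headings and the sample size, and it calls the within-group comparisons post hoc. That is correct: there is one primary test at 0.05 and its error rate is not inflated. Only the significance rule fails to separate them.

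**This belongs to the analysis plan.** A threshold of 0.05 is conventional, does not say that P-values are unadjusted, and could be refined in a document not shown here. Silence on adjustment would indeed be no finding. What remains is that the protocol states an unqualified rule, gives no exploratory label, and attaches directional hypotheses to many secondary outcomes.

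**The count is soft.** This stands. The food frequency questionnaire, the frozen samples and the intended child follow-up need not become efficacy tests, and some nulls may be false; the Discussion cites evidence that pelvic floor exercises reduce urinary incontinence. The table therefore shows a range.

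**Either-direction figures overstate chance benefits.** Also right. In favour of exercise the expected number is half, and at the assumed correlations of 0.3 and 0.5 at least one chance benefit is less likely than not for every m shown.

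A reader might infer two stronger points that the protocol does not support:
- *That a chance secondary finding could carry a routine-care recommendation after a null primary.* The abstract says "If the program proves effective in reducing gestational weight gain and adverse pregnancy outcomes, such programs should be considered as part of routine pregnancy care", which joins the two conditions. The Discussion separately makes consideration for regular care depend on reduced gestational weight gain. Under either sentence a null primary does not meet the stated condition. The hope expressed in the Discussion, "In addition to effects on weight gain, we hope to see a reduction in other pregnancy complications", does not alter it.
- *That a null primary is likely unless the true effect is near 6 kg.* The SD is not stated; 59 per group for a 6 kg difference at 90% power implies about 10 kg. The standard error is then 10 × √(2/59) = 1.84 kg, and power falls below 50% only for true differences under about 1.96 × 1.84 = 3.6 kg.

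**Conclusion.** The point holds as a weakness in how the significance rule is fixed. Applied as written, it would produce some claims of significance by chance among the secondary outcomes: 2.5 expected at m = 50, of which 1.25 favour exercise. These expected numbers depend on the count, on two-sided testing and on all nulls being true, but not on correlation. The probabilities of at least one (92%, 81% and 62% in either direction; 72%, 45% and 32% favouring exercise) rest also on the assumed correlations, and the first of each set is the independence case. Within-group and exercise-split comparisons would add to the totals. The primary comparison and the stated conditions for considering routine care are not affected. The point is worth correcting because it changes what may be concluded from the secondary results and needs only a change of wording.

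**What to change.** In Statistical methods, replace the general threshold with wording to this effect: the significance criterion of P below 0.05 applies to the intention-to-treat comparison of gestational weight gain; secondary outcomes, within-group changes and the splits by actual exercise are exploratory and are reported as estimates with 95% confidence intervals and nominal P-values.

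The intervals are already planned, so sample size, data collection and the primary test stay as they are. The cost is one or two sentences, and the investigators give up calling nominal secondary findings significant.

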#### Discussion

Maternal obesity is regarded a high-risk obstetric condition and is associated with pregnancy complications and adverse outcomes [2]. In addition, there is increasing evidence that gestational weight gain may be an important predictor of the women's risk of subsequent obesity and diabetes. It has therefore been proposed that pregnancy is a unique period of time with regard to changing women's behaviour [41]. In the present study, we aim to prevent excess gestational weight gain and obesity related pregnancy complications through regular exercise training throughout pregnancy.

A recent study showed that approximately 60% of overweight women gain more than recommended during pregnancy, and as gestational weight gain associates with weight retained during the postpartum period [3], excess gestational weight gain could accelerate the obesity epidemic. Thus the prevention of weight gain in overweight and obese pregnant women is an important public health issue. Further, maternal obesity is associated with a number of adverse outcomes during and

after pregnancy, such as gestational diabetes, preeclampsia, caesarean delivery and children large for gestational age [2]. The risk for gestational diabetes is increased 2-3 fold with obesity, and fetuses of obese mothers have higher risk of developing insulin resistance in utero [42]. Greater maternal gestational weight gain has also repeatedly been found to associate with offspring adiposity in childhood [4] and in early adulthood [5]. As obese children have elevated levels of inflammatory markers related to cardiac disease manifested later in life [43], they will be at increased risk for subsequent cardiovascular disease. Importantly, there are indications in the recent literature that the prenatal environment plays a role for children obesity, independent of genetic predisposition and shared eating habits [44,45].

Strengths of our study include the thorough testing that will be done of the women as well as their offspring; investigating possible effects of exercise training on weight gain, endothelial function, insulin resistance, cardiac function, incontinence problems, lumbopelvic pain, and psychological wellbeing. In addition we collect comprehensive information on physical activity, using both subjective and objective measurements (questionnaire and armband activity registrations, respectively), as well as on dietary habits. Also regarded as a strength of the study, is the composition of the exercise training program, comprising both endurance training, general strength training and specific pelvic floor exercises.

A possible weakness of our study is that it could be underpowered for small differences in gestational weight gain between groups. Also, we think that women who like to participate in this kind of study are motivated for exercise and thereby that some of the women in the control group will do regular exercise training on their own. Such cross-over from the control group would potentially lead to smaller between-group differences.

The results from our study will give grounds for giving advice as well as organizing exercise training groups for women with obesity entering pregnancy. If women randomized to training manage to reduce their gestational weight gain compared to controls, such programs should be considered as part of the regular pregnancy care for this high-risk obstetric group.

In addition to effects on weight gain, we hope to see a reduction in other pregnancy complications. Our study will investigate the ability of regular exercise training to prevent gestational diabetes mellitus, as well as the effect on serum biomarkers associated with insulin resistance and inflammation. Previous work have found that exercise training may reduce lumbopelvic pain [46,47], however, a preventive effect of exercise during pregnancy remains unclear. Pregnancy and childbirth may also cause urinary and fecal incontinence, and obesity is an additional risk factor. The average prevalence of

urinary incontinence during pregnancy and after delivery is 30-40%, and of fecal incontinence after delivery 4-5% [48]. Specific pelvic floor muscle exercises in pregnancy and post partum reduce urinary incontinence, while the preventive effect on fecal incontinence is less documented [49].

Although observational evidence is quite consistent regarding the association between large gestational weight gain and offspring adiposity, the evidence for causality is still lacking. It is possible that the intrauterine experience of infants born to mothers who gain a lot when pregnant programs long-term weight regulation, or the maternal weight gain could just be a marker of other, shared causes of both maternal and offspring weight [50]. The optimal way to explore the impact of the intrauterine exposure upon child adiposity, would be to randomized women to usual care or to an effective intervention limiting gestational weight gain, and then to follow the infants longitudinally. To our knowledge, no such adequately powered, randomized trial has been done to investigate the possible causality between excess gestational weight gain and child obesity. The randomized trial we propose here will provide evidence for such a causal relationship.

#### List of abbreviations

ETIP: Exercise training in pregnancy; BMI: Body mass index; LGA: Large for gestational age; SGA: Small for gestational age; HOMA-IR: Insulin resistance homeostasis model assessment; DEXA: dual energy x-ray absorptiometry; 2D: two-dimensional; 3D: three-dimensional; SF-8: Short form 8; LV: left ventricular; AV-plane: atrioventricular plane

#### Acknowledgements and Funding

This trial is funded by the Norwegian Fund for Postgraduate Training in Physiotherapy (TM), and the Norwegian Research Council (CBI), the Harvard Pilgrim Health Care Institute (EO). Study design and conduction, writing of manuscript and submission for publication is done independently of the funding body/bodies.

# Competing interests

The authors declare that they have no competing interests.

Received: 27 January 2011 Accepted: 17 June 2011

Published: 17 June 2011

**Submit your next manuscript to BioMed Central and take full advantage of:**

- Convenient online submission
- Thorough peer review
- No space constraints or color figure charges
- Immediate publication on acceptance
- Inclusion in PubMed, CAS, Scopus and Google Scholar
- Research which is freely available for redistribution

Submit your manuscript at  
[www.biomedcentral.com/submit](http://www.biomedcentral.com/submit)

[figure not shown]

Supplement: S2 Protocol — (PDF) [file pone.0197334.s002.pdf]
